## Abstract

**Background:**

Ankle-Foot-Orthoses with a ventral shell, also known as Floor Reaction Orthoses (FROs), are often used to reduce gait-related problems in children with spastic cerebral palsy (SCP), walking with excessive knee flexion. However, current evidence for the effectiveness (e.g. in terms of walking energy cost) of FROs is both limited and inconclusive. Much of this ambiguity may be due to a mismatch between the FRO ankle stiffness and the patient’s gait deviations.

The primary aim of this study is to evaluate the effect of FROs optimised for ankle stiffness on the walking energy cost in children with SCP, compared to walking with shoes alone. In addition, effects on various secondary outcome measures will be evaluated in order to identify possible working mechanisms and potential predictors of FRO treatment success.

**Method/Design:**

A pre-post experimental study design will include 32 children with SCP, walking with excessive knee flexion in midstance, recruited from our university hospital and affiliated rehabilitation centres. All participants will receive a newly designed FRO, allowing ankle stiffness to be varied into three configurations by means of a hinge. Gait biomechanics will be assessed for each FRO configuration. The FRO that results in the greatest reduction in knee flexion during the single stance phase will be selected as the subject’s optimal FRO. Subsequently, the effects of wearing this optimal FRO will be evaluated after 12–20 weeks. The primary study parameter will be walking energy cost, with the most important secondary outcomes being intensity of participation, daily activity, walking speed and gait biomechanics.

**Discussion:**

The AFO-CP trial will be the first experimental study to evaluate the effect of individually optimised FROs on mobility and participation. The evaluation will include outcome measures at all levels of the International Classification of Functioning, Disability and Health, providing a unique set of data with which to assess relationships between outcome measures. This will give insights into working mechanisms of FROs and will help to identify predictors of treatment success, both of which will contribute to improving FRO treatment in SCP in term.

**Trial registration:**

This study is registered in the Dutch Trial Register as NTR3418.

## Background

With an incidence of 2–3 per 1000 living births, Cerebral Palsy (CP) is the most frequent cause of motor disorders in childhood in Western countries
[1]. Spastic motor disorders are most common in children with CP, with symptoms of spasticity, muscle weakness and decreased selective motor control
[2], often causing limitations in mobility
[3], which may lead to a restricted participation in everyday life
[4].

Although more than half of all children with bilateral spastic CP (SCP) walk independently with or without an assistive device
[5], most experience mobility-related problems, such as reduced gait speed and/or an increased walking energy cost
[6-12]. These problems are often caused by gait deviations
[13-16], which can be corrected by prescribing ankle-foot orthoses (AFOs). An AFO imposes a mechanical constraint on the ankle, either to compensate for loss of function
[17-19] or to counteract an excess of function
[20,21]. An AFO therefore acts by applying control to the ankle and foot and, dependent on its design, it can indirectly stabilise the knee and hip joints
[22]. As such, AFOs aim to improve, i.e. normalise joint kinetics, joint kinematics and spatio-temporal parameters
[17,23-26]. Improvements in joint kinetics and kinematics have been shown to be closely coupled to an improved walking energy cost, which leads to benefits in walking ability; an effect also noted in the context of orthotic interventions
[23,25-27]. This applies especially to children who walk with excessive knee flexion in midstance, since this walking pattern is particularly energy consuming
[9,10] and these children are liable to show deterioration in walking ability in (pre-) puberty
[28,29].

A variety of AFO types are available, depending on the specific gait deviations of the child. For children who walk with excessive knee flexion, orthoses with a ventral shell, also known as Floor Reaction Orthoses (FROs), are commonly prescribed
[20]. Although FROs are widely used in SCP, evidence supporting their effectiveness is so far lacking. The decision-making process leading to FRO prescription is still based on expert opinion and experience (i.e. a trial-and-error approach), resulting in differences in treatment paradigms with respect to both the indication and the mechanical construction of FROs
[30,31]. This is reflected in current literature, as studies have shown that wearing an FRO can be effective in decreasing walking energy cost, but may also have no effect
[32] or even be adverse in some children in terms of walking energy cost or gait speed
[26,32].

This variation in FRO effectiveness might be partly explained by the match of the mechanical properties of the orthosis to a patient’s specific gait deviations. Research in adults with neurological disorders has shown that walking energy cost with a typical spring-like AFO could be optimised by choosing the correct AFO ankle stiffness
[33], suggesting that there may be an optimal match between a patient’s characteristics and the mechanical properties of an AFO. A similar principal might also apply to FROs.

A conventional FRO is a rigid type of AFO, and includes a ventral shell and a rigid footplate. The biomechanical mechanism of an FRO is to create a knee-extensor moment during midstance and terminal stance, by shifting of the ground reaction force forward
[21]. Although an FRO might be effective in this respect, ankle push-off power is obstructed by an impeded plantar flexion in terminal stance and preswing. To enhance push-off power, a more spring-like FRO could potentially be beneficial, since it could store energy at the beginning of the stance phase that is released and returned in preswing. Achieving a sufficiently high stiffness to counteract knee flexion while including the potential benefit of spring-like properties in terms of walking energy cost may result in an optimal FRO stiffness based on the least compromise between these two goals.

Designing and evaluating the efficacy of such an optimal FRO requires an evaluation of the effects of different degrees of FRO ankle stiffness on various aspects of gait, i.e. function, mobility and participation. This implies a need for a set of outcome measures that covers all domains of the International Classification of Functioning, Disability and Health (ICF)
[34]. Evaluating the effects of an intervention on more than one of the ICF domains will provide insights into mutual relations, thereby aiming to identify possible working mechanisms
[35], which will contribute to improved FRO treatment.

FRO treatment could be further improved by identifying those children who could benefit from FROs
[30]. Rogozinski et al.
[21] explored clinical examination parameters that might explain the efficacy of FROs in CP children walking with excessive knee flexion. They found a strong, negative correlation between knee and hip flexion contractures and peak knee extension, achieved during walking with an FRO. Other studies have shown that child characteristics and environmental factors predict the response to rehabilitation interventions, such as Botulinum toxin A injections
[36-38] and surgery
[39-41]. Specific patient characteristics might also be relevant predictive factors for FRO efficacy.

In summary, evidence supporting the efficacy of FROs in children with SCP walking with excessive knee flexion remains inconclusive. Understanding of both the underlying working mechanisms and the factors predictive of treatment success is still lacking. Therefore, this project has two main goals:

1. To study the effect of an FRO optimised for ankle stiffness on walking energy cost in children with SCP walking with excessive knee flexion, compared to walking with shoes alone.

2. To identify the possible working mechanisms of an FRO, and the predictors for success of FRO treatment in children with SCP, walking with excessive knee flexion.

## Methods

### Design

A pre-post experimental study consisting of two repeated measurements, i.e. at baseline, T0, walking with shoes only (control), and at 12–20 weeks follow-up, T2_Kopt_, walking with an optimised FRO (case) will be performed to evaluate FRO efficacy in children with SCP (Figure
1). The study protocol has been approved by the Medical Ethics Committee of the VU University Medical Center in Amsterdam. 

**Figure 1 F1:**
[figure not shown]
**Schematic representation of the study design. **Following baseline measurements (T0), the subject’s will be prescribed an interventional FRO. The stiffness of this FRO will be varied (rigid, stiff and flexible) and the order of FRO stiffness will be block randomised. Accommodation time for each stiffness will last 4–8 weeks, after which effects will be evaluated (T1_K1_, T1_K2_, and T1_K3_). Following these evaluations, an optimal FRO for the subject will be selected. Follow-up measurements (T2_Kopt_) will be carried out at 12–20 weeks. B=Block; FRO= Floor Reaction Orthosis; K=AFO stiffness; K_1_, K_2_, and K_3_ represent either rigid, stiff or flexible stiffness configurations.

Following completion of study enrolment, baseline measurements (T0) will be performed barefoot, with shoes only and with the subject’s current orthosis (if applicable). Stiffness (K) of the new FRO will be varied into three configurations: rigid, stiff, and flexible. A balanced block randomisation will be applied for six possible sequences of stiffness configurations, to ensure that the same number of patients is allocated to each sequence. Every configuration will be worn for an accommodation period of four to eight weeks, after which FRO efficacy will be evaluated (T1_k1_,T1_K2_ and T1_K3_). An analysis of the evaluation of all FRO configurations will allow the selection of the stiffness with the maximal benefit for a particular subject, referred to as the subject’s optimal FRO (the selection procedure is explained further below). Following this selection, the optimal FRO will be worn for twelve to twenty weeks, after which the follow-up measurements (T2_Kopt_) will be taken.

### Participants

#### Inclusion and exclusion criteria

Our aim is to include 32 children with SCP (Gross Motor Function Classification Score
[42] (GMFCS) levels I, II and III [provided that the child is able to perform a 3D-gait analysis without walking aids]) who are candidates for a (new) FRO. Children will be recruited from the outpatient clinic of the VU University Medical Center, Amsterdam and affiliated rehabilitation centres.

Study information will be provided to potential participants in the form of a patient information letter and a brochure. Patients and parents willing to participate will be contacted by the primary investigator (YK), who will verify inclusion and exclusion criteria (Table
1). When a patient meets the inclusion criteria, oral and written informed consent will be obtained from both parents, and from children aged 12 years and older, in accordance with the declaration of Helsinki. 

**Table 1 T1:** Inclusion and exclusion criteria

	
**Inclusion criteria**	
	Spastic CP;
	6-14 years;
	A gait pattern characterised by excessive knee flexion (jump gait, apparent equinus or crouch gait) [42];
	GMFCS I, II, or III (provided that the patient is able to walk independently for at least 15 meters)
**Exclusion criteria**	
	Any orthopaedic surgery or other surgical interventions that might influence mobility in the past 6 months;
	Botulinum toxin A injections in the past 3 months, Intrathecal Baclofen therapy in the past 6 months, or SDR in the past year;
	Impairments that could contraindicate fitness testing;
	Plantar flexion contractures or knee contractures >10° or hip endorotation > 20° in midstance;
	Other medical conditions influencing mobility;
	Severe behavioural problems;

GMFCS: Gross Motor Function Classification System [43]; SDR: Selective Dorsal Rhizotomy.

#### Sample size

The sample size will be based on a power analysis of the expected changes (i.e. T0 versus T2) in the primary outcome, walking energy cost [J^-1^⋅kg^-1^⋅m^1^. According to literature, walking energy cost in children with CP may be 30-50% higher than in healthy children
[10-12]. SCP children with GMFCS levels I, II and III show a mean net EC of 5.02 (±1.70) J^-1^⋅kg^-1^⋅m^1^[26]. A reduction of 25% in this value (≈1.26 J^-1^⋅kg^-1^⋅m^1^) is considered to be a clinically significant change
[25,26]. Assuming a power of 80% and a significance level of 0.05, detecting a clinically significant change will require a sample size of 29 children
[44]. Allowing for a dropout of approximately 10%, a sample size of 32 will be sufficient.

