#### Evaluation of FRO efficacy

Evaluation of the efficacy of a subject’s optimal FRO will be based on analyses of pre/post-intervention differences in primary and secondary outcome measures. The pre-intervention (control) condition will be for shoes only. Mean data for these measurements (assessed at T0) will be compared to follow-up measurements (T2_Kopt_), using paired sample t-tests.

To identify working mechanisms, multivariate linear regression analyses will be applied to investigate which of the changes in gait biomechanics are associated with changes in walking energy cost (model 1) and daily activity (model 2). First, a univariate regression analysis (ANOVA) will be performed to determine which factors are significantly associated with changes in the biomechanics of gait (p≤0.1), followed by the analysis of significant factors (p≤.05) in a multivariate regression analysis model.

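### The 29 children match the planned paired t-test only if baseline and follow-up energy cost are almost uncorrelated within a child, an assumption the protocol neither states nor justifies

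*Protocol article*

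**What the plan says.** All references are to the protocol article.

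- **Design:** the study is described as "A pre-post experimental study consisting of two repeated measurements", with shoes only at T0 and the optimised orthosis at T2. There is no parallel group.
- **Evaluation of FRO efficacy:** the T0 data "will be compared to follow-up measurements (T2_Kopt_), using paired sample t-tests".
- **Sample size, target:** the number is to rest on a "power analysis of the expected changes (i.e. T0 versus T2) in the primary outcome", that is, on a within-child change.
- **Sample size, inputs:** the only measure of variability is cross-sectional: "SCP children with GMFCS levels I, II and III show a mean net EC of 5.02 (±1.70"). The target is given as "A reduction of 25% in this value (≈1.26" in the same units), and the error rates as "Assuming a power of 80% and a significance level of 0.05".
- **Sample size, result:** "detecting a clinically significant change will require a sample size of 29 children", raised to 32 for a dropout of about 10%.

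The section gives no SD of the T0 to T2 change, no within-child correlation, no sidedness and no named formula. It cites a reference for the calculation.

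**The concern.** In a paired t-test, variation between children cancels out and precision depends on the SD of the within-child change. The protocol instead gives the spread of energy cost across children at one measurement. The two are linked by the T0 to T2 correlation, about which the protocol is silent. If 29 comes from a calculation that ignores pairing, then the stated 80% is not the power of this design, and 29 is not the number this design requires.

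Two things are at stake. The only justification given for the sample size would not describe the planned analysis, in a study where each child wears three stiffness configurations and then the selected one for months. Readers would also misjudge the trial's sensitivity: a paired analysis of 29 could reach significance for a change clearly below the 25% that the protocol itself calls clinically significant.

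**Working it through.** **Inputs.** From Sample size: SD 1.70, difference 1.26 (25% of 5.02 = 1.255), power 80%, significance level 0.05. From Design and Evaluation of FRO efficacy: one group, paired t-test. Assumed because not stated: a two-sided test, equal SDs at T0 and T2, and a correlation r between the two visits, shown as a range.

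**Step 1: reproduce 29.** For two independent groups (normal approximation), n per group = 2 × (z₀.₉₇₅ + z₀.₈₀)² × (SD/difference)².

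- 2 × 7.849 × (1.70/1.26)² = 28.6, rounded up to **29 per group**. With 1.255 the result is 28.8, also 29.
- The one-sided version gives 22.5, so 23.
- The exact two-sample t version gives 29.6, so 30.

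The two-sided normal approximation matches the printed figure.

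**Step 2: try the paired formula with 1.70 as the SD of change.** n = 7.849 × (1.70/1.26)² = 14.3, so 15; exact t gives 16.3, so 17. One-sided versions give 12 (normal) and 13 (exact t). None gives 29.

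**Step 3: find what a paired calculation would need to give 29.** SD of change = 1.70 × √(2(1 − r)). At r = 0 this is 2.40, and 7.849 × (2.40/1.26)² is again 28.6 (using the unrounded 2.404). This is algebraically the same as the formula in Step 1. So 29 arises either from two independent groups or from a paired comparison with zero correlation.

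**Step 4: calculate the planned test.** Exact two-sided paired t-test, significance level 0.05, difference 1.26. The detectable change at 29 is 0.539 × SD of change, and its percentage is of 5.02.

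| Assumed r | SD of change | Power with 29 completers | N for 80% power | Change detectable with 80% power at 29 |
|---|---|---|---|---|
| 0 | 2.40 | 78% | 31 | 1.30 (26%) |
| 0.3 | 2.01 | 90% | 23 | 1.08 (22%) |
| 0.5 | 1.70 | 97% | 17 | 0.92 (18%) |
| 0.7 | 1.32 | 99.9% | 11 | 0.71 (14%) |

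**Step 5: find where 29 completers give exactly 80%.** This needs an SD of change of about 2.34, which implies r = 1 − 2.34²/(2 × 1.70²) ≈ 0.05.

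**The case against.** **The formula is not named.** The protocol cites a source for its calculation and says that it concerns the T0 to T2 change. A reader might infer that a two-group formula was used by mistake. The documents do not establish this: a paired calculation with zero correlation gives the same 29. This objection stands, and the point is worded accordingly. It does not remove the problem, because neither route is stated or justified, and the second assumes that two measurements of the same child are unrelated.

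**The error is on the safe side.** Over r = 0.3 to 0.7, power for 1.26 is 90% to 99.9%. The number of children and the primary test need no change, and the same children also serve the regression models. This also stands, and it limits the severity.

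**The correlations are assumptions.** T0 and T2 are at least 24 to 44 weeks apart (three periods of 4–8 weeks plus 12–20 weeks), in children aged 6–14 whose response to orthoses is described as variable. Both could lower r. The table rows are therefore scenarios, not predictions.

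**Two stronger readings that the documents do not support.**

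- A reader might take the 78% at r = 0 as a sign that the trial is underpowered. That shortfall from 80% is only the difference between the exact t-test and the normal approximation.
- A reader might set 1.26 against the statement that "walking energy cost in children with CP may be 30-50% higher than in healthy children" and conclude that the target removes nearly all of the excess cost. The 30–50% and the mean of 5.02 come from different sources, and nothing shows that they share a population or a gross or net definition. The trial also enrols only children with excessive knee flexion, which the Background calls especially energy consuming. No ceiling on the effect can be derived from these figures.

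**Conclusion.** The point holds, at moderate severity. The stated 80% power and the stated requirement of 29 do not follow for the planned paired t-test on any assumption that the protocol gives. They would be right only with an SD of change of about 2.34, which is a correlation of about 0.05 if the SDs are equal at both visits.

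At any plausible positive correlation the trial has more power for 1.26 than it claims, so the primary comparison is not at risk. What is wrong is the justification of the number and the implied sensitivity. At r = 0.5, 17 children would meet the stated criterion, and 29 would detect 0.92 (18%) with 80% power. A significant result may thus lie below the protocol's own 25% threshold.

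The mismatch between inputs and test comes directly from the protocol's text. The size of the power difference rests on a two-sided test, equal SDs at the two visits and the assumed range of r.

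**What to change.** Keep 32 children. Rewrite the Sample size paragraph as a two-sided paired calculation that:

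1. states the assumed SD of the T0 to T2 change in net energy cost, with its source (test-retest or earlier pre-post data), or a range of correlations such as 0.3 to 0.7 if no source is available;
2. gives the resulting power for a change of 1.26 with 29 completers;
3. gives the change detectable with 80% power at 29 completers, set beside the 25% threshold.

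Delete the statement that 29 children are required for 80% power. The cost is one paragraph of wording, with no more patients and no change to the design or the primary test.

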### Investigational AFO

Investigational FROs will be composed of prepreg carbon, manufactured using the Mälmo-technique (Otto Bock HealthCare GmbH, Duderstadt, Germany). For fair evaluation of efficacy, the investigational FRO will be fabricated with a rigid footplate. To further ensure a fair comparison, tuning of the FRO-footwear combination following the Owen method will be carried out for each configuration
[45].

Investigational FROs will be fabricated with an integrated Neuro Swing® system hinge (Fior & Gentz, Lüneberg, Germany), which is available in different sizes. The size of the hinge is dependent on the body weight and length of the patient. For this study, it is expected that only the 14mm and 16mm hinges will be used. The hinge holds an anterior and posterior shaft, and comes with a package of five springs, each with a different degree of stiffness. Ankle stiffness can be adjusted within the same orthosis, using different spring forces towards plantar and dorsal flexion. In this study, the hinge will be prepared in three configurations: rigid, stiff and flexible. The rigid configuration (i.e. ±4.3 Nm/deg) will entirely prevent dorsal or plantar flexion. For the stiff and flexible configurations, the spring force for dorsal flexion will be varied using the strongest spring (i.e. ±1.2 Nm/deg [14mm] and ±2.4 Nm/deg [16mm]) and the second strongest spring (i.e. ±0.5 Nm/deg [14mm] and ±1.0 Nm/deg [16mm]), respectively. The spring force towards plantar flexion will be very compliant (i.e. ±0.01 Nm/deg [14mm] and ±0.04 Nm/deg [16mm]) for both configurations.

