#### Other outcomes

Other study outcome measures will include 1) the patient’s personal treatment goals, measured with Goal Attainment Scaling (GAS), 2) treatment adherence, assessed with a motivation diary and with the @monitor
[55], 3) satisfaction with the FRO, as perceived by the patient and parents and 4) FRO stiffness, measured with BRUCE, which is a recently developed device for measuring mechanical AFO properties
[56].

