#### Identifying prognostic factors

Multivariate regression analysis will also be applied to investigate to what extent child characteristics and FRO stiffness represent determinants for success of FRO treatment, defined as decreased walking energy cost (model 1), improvement in daily activity (model 2) and positive GAS scores (model 3). Initially, a univariate regression analysis (ANOVA) will be performed to determine which factors are significantly associated with FRO treatment outcomes (p≤0.1). Significant factors (p≤.05) will then be included in a multivariate regression model. Model analysis will include factors such as level of physical fitness, baseline disease characteristics, gait pattern, level of functional mobility, environmental factors and FRO characteristics.

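### FRO stiffness in Nm/deg is partly a marker of body size in the determinant models, and the screening rule does not guarantee adjustment for it

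*Protocol article*

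**What the plan says.** All device figures are in the protocol article under Investigational AFO. On hinge choice: "The size of the hinge is dependent on the body weight and length of the patient", and "it is expected that only the 14mm and 16mm hinges will be used". The three settings are:

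- Rigid: "The rigid configuration (i.e. ±4.3 Nm/deg) will entirely prevent dorsal or plantar flexion", one value that is not split by hinge.
- Stiff, towards dorsal flexion: "using the strongest spring (i.e. ±1.2 Nm/deg [14mm] and ±2.4 Nm/deg [16mm"].
- Flexible, towards dorsal flexion: "the second strongest spring (i.e. ±0.5 Nm/deg [14mm] and ±1.0 Nm/deg [16mm]), respectively".

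The plantar-flexion spring is "very compliant (i.e. ±0.01 Nm/deg [14mm] and ±0.04 Nm/deg [16mm]) for both configurations".

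Under Identifying prognostic factors, a regression across children is to examine "to what extent child characteristics and FRO stiffness represent determinants for success of FRO treatment". Success is judged on walking energy cost, daily activity and GAS. Factors are screened one at a time at p≤0.1, and those significant at p≤.05 go into the multivariate model. The section does not say whether stiffness enters as the label, as Nm/deg or in a scaled form. Other outcomes lists "FRO stiffness, measured with BRUCE, which is a recently developed device for measuring mechanical AFO properties", with no scaling to body size. Effect modifiers includes demographic variables, but weight, height and hinge size are not named as model terms.

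**The concern.** The determinant models serve the second of the study's two main goals: finding which children benefit and how that relates to stiffness. This comparison runs between children, so stiffness must be separable from the children's other characteristics. The device description works against that. A larger child gets the larger hinge, and in that hinge two of the three settings are twice as stiff. A stiffness coefficient can then carry an effect of body size, or of age through size.

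The rule for building the model leaves this open. A covariate that fails its own univariate screen is dropped, and in about 29 children a real confounder can easily fail. At stake is the guidance on which child needs which stiffness: an apparent stiffness effect could be a size effect and would not carry over between small and large children.

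**Working it through.** **Number of children.** The plan's 29 can be reproduced from Sample size (difference 1.26, SD 1.70, 80% power, 0.05, two-sided assumed): 2 × (1.70 × (1.960 + 0.842) / 1.26)² = 28.6, rounded up to 29. It is used here only as the number available for the determinant models.

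**Nominal stiffness by hinge (Investigational AFO).**

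| Setting | 14 mm | 16 mm | Ratio 16/14 |
|---|---|---|---|
| Rigid | 4.3 | 4.3 | 1.0 |
| Stiff | 1.2 | 2.4 | 2.0 |
| Flexible | 0.5 | 1.0 | 2.0 |
| Plantar-flexion spring | 0.01 | 0.04 | 4.0 |

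Flexible in the 16 mm hinge is 1.0/1.2 = 0.83 of stiff in the 14 mm hinge.

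**Correlation of Nm/deg with hinge size.** Assumptions: half the children on each hinge, and the chosen setting unrelated to hinge. With equal hinge groups, r = (difference in hinge means / 2) / (overall SD).

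- No child in rigid, stiff and flexible equally common: means 0.85 and 1.70, overall SD 0.698, r = 0.425/0.698 = 0.61.
- Equal thirds: means 6.0/3 = 2.00 and 7.7/3 = 2.57, overall SD 1.536, r = 0.283/1.536 = 0.18.
- 20% rigid: r = 0.25. 50% rigid: r = 0.13.
- Among children in the stiff setting alone: r = 1.0.

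With 25 to 75% of children on the 16 mm hinge, r is 0.50 to 0.62 without rigid and 0.15 to 0.18 with equal thirds.

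**Consequence for the test.** Simulation: 29 children, 4,000 replicates, no true stiffness effect, outcome differing between hinge groups by 0.5 to 1.0 SD, test at 0.05.

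| Chosen settings | Nm/deg alone | Label alone | Nm/deg with hinge size in the model |
|---|---|---|---|
| No rigid | 12.5–29.6% | 5.0–5.5% | 5.1–5.3% |
| Equal thirds | 5.7–6.9% | 4.7–4.8% | 4.8–5.3% |

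**Does dividing by body mass solve it?** The documents give no weights, so these are assumed. With equal thirds and 20 kg (14 mm) against 40 kg (16 mm), stiff is 0.060 and flexible 0.025 Nm/deg/kg in both hinges, but rigid is 0.215 against 0.107. The correlation of scaled stiffness with hinge size is then −0.27, larger in size than the +0.18 for unscaled stiffness. At 25 and 40 kg it is −0.15, and at 30 and 40 kg −0.03. Without rigid, the same three weight pairs give 0.00, +0.26 and +0.43. Scaling moves the link with size about; it does not reliably remove it.

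**The case against.** The strongest reply is that the article fixes no wrong metric. It names stiffness as a candidate and leaves the coding open, which an article may leave to a fuller plan. That stands as far as coding goes: silence on the metric is not the point. What the article does fix is hinge-dependent stiffness, stiffness as a between-child determinant, and retention of covariates by screening alone. Together these leave adjustment to chance.

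Second, demographic variables and child characteristics are candidates, so body size could enter. It could, but only by passing the screen.

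Third, bias also needs body size to be related to the outcome. This is a real limit. Under Primary outcome, the net non-dimensional energy cost is described as largely independent of mass, height and age, so the risk is lower there. No such statement covers daily activity or GAS.

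Fourth, a hinge chosen by weight and length may already act as size scaling. At the assumed 20 and 40 kg it does so exactly for stiff and flexible, but not for rigid, and the true weights are unknown.

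A reader might infer that the configuration label is itself confounded with body size. The documents do not support that: each child wears all three settings in balanced order and the optimum is chosen within the child, so the label is not tied to size by design. A reader might also worry that a child's hinge size changes during the study and alters what a label means. Nothing in the documents suggests it; stiffness is adjusted within the same orthosis.

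**Conclusion.** The concern holds in a limited form. Stiffness in Nm/deg, nominal or measured with BRUCE, is partly a marker of body size in the determinant models. The link is strong if few children end in rigid (r about 0.5 to 0.6) and weak if the settings are equally common (about 0.15 to 0.18). The label has a different and milder defect: stiff and flexible each pool nominal values a factor of two apart. Screening does not guarantee the adjustment that would deal with this.

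The size of any bias rests on things the documents do not give: the mix of hinges, the mix of chosen settings, and whether body size affects each outcome. It is a foreseeable risk, not a demonstrated bias. It is confined to the models under Identifying prognostic factors. The paired T0–T2 comparison and the within-child choice of setting are unaffected, because each child is compared with itself.

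**What to change.** Under Identifying prognostic factors, add that whenever FRO stiffness enters a determinant model, hinge size (or body mass) is forced into that model whatever its screening result, and that the stiffness coefficient is interpreted only with this adjustment. Stiffness scaled to body mass may be shown as a sensitivity analysis, but not in place of the covariate. No device setting or selection rule is touched.

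The cost is a sentence and one degree of freedom: with 29 children and stiffness as the only other term, residual degrees of freedom fall from 27 to 26. Adjustment also widens the standard error of the stiffness coefficient by about √(1/(1 − r²)): 1.02 at r = 0.18 and 1.26 at r = 0.61. That loss reflects how little the data can separate stiffness from size when few children end in rigid. Hinge size needs no extra measurement, and weight and length must be known to choose it.
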